### Statistics

The data processing methods will be similar to those described in the MOTANA protocol [23]. For each patient and each MNS, the maximal value of ERD and ERS max will be, respectively, selected in (0.25;0.5) seconds and (2;4) seconds after stimulation, in accordance with the literature [24,37]. An average over the ERDs max and ERSs max will be performed for each concentration. These 2 values will be, respectively, compared with average ERDs max and ERSs max obtained in the preoperative rest condition with a Student *t* test (*P*<.05). To visualize the event-related spectral perturbations with the EEGLAB toolbox, a surrogate permutation test will be used (*P*<.05; 2000 permutations). In addition to the permutation test, we will apply a false discovery rate correction to show the difference in MNS effect during different concentrations of propofol.

In addition to the event-related spectral perturbation analyses, we will apply 4 different offline machine learning algorithms to detect the MNS at the cerebral level. To do this, these algorithms are based on 4 classification methods in a 4-fold cross-validation scheme. The classification score will be computed for the MNS versus the rest class. Each trial will be segmented into a motor task time window and a resting time window, both lasting 2 seconds. The motor task time window will begin 0.5 seconds after the MNS, and the resting phase time window will begin 3 seconds before the MNS. The first classification method is a linear discriminant analysis method using a common spatial pattern [38] (referred to as common spatial pattern+linear discriminant analysis). For the next 3 classifiers, we will use classifiers that are based on Riemannian geometry. Riemannian geometry-based methods have the advantage of being immune to linear transformations and to be particularly efficient for the detection of motor intentions. For the statistical differences in the latency and topographic voltage of the SEP components, similar permutation tests and post hoc tests will be applied.

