The patients’ testimonies show that the first reaction during an AAGA is usually to move to alert the medical staff [2,17]. Unfortunately, during most surgeries, the patient is curarized, which causes neuromuscular block and prevents any movement. Detecting movement intention (MI) is possible by analyzing EEG signals from the motor cortex with a brain-computer interface (BCI). This is based on previous evidence demonstrating that simple MIs are characterized by power spectrum variations (ie, event-related (de)-synchronization called ERD/ERS) in the EEG mu (7-13 Hz) and beta (15-35 Hz) bands over the motor cortex [18] and that electrical stimulation of the median nerve also induces changes in the cortical activity [19,20], which are visible in the EEG signal and which are similar to an MI [21,22]. Interestingly, our preliminary results suggested that when a hand MI coincides with median nerve stimulation (MNS), the ERD/ERS is considerably reduced, and thus the MI can be detected much better by machine learning techniques than an MI without MNS [23-26]. The originality of this BCI paradigm is to exploit this MNS-induced phenomenon to accurately detect the patient’s motor intention during an AAGA. Based on these previous results, we envisage a routine procedure where the anesthetized patient is stimulated by electrical pulses delivered at the median nerve position at the wrist, while a BCI device analyzes the ERD and ERS modulations over the motor cortex to detect the intention of movement of the patient. Our previous clinical trial (MOTANA protocol [23]) also includes a condition with MNS and another with MNS accompanied by MI for 3 concentrations of propofol (0, 0.5 µg/mL, and 1 µg/mL). The preliminary results (n=15) highlighted the advantage of a BCI based on MNS from both a functional and an accuracy point of view. First, MNS intrinsically provides a trigger to know when to analyze the signal. Second, the classification accuracy of an MNS-based BCI appeared to be way better than that of a BCI aiming to discriminate a motor imagination from a resting state. More precisely, an MNS-based BCI detected the MI state 15% more accurately. For several subjects, the use of MNS improves performance by more than 20% compared to a standard method [22,25].

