### EEG Data Acquisition

Motor EEG signals will be collected through the OpenViBE software platform with eego mylab system (ANT neuro) 64-EEG channels, covering the entire scalp at 16,000 Hz and 1 external channel placed on the dorsum of the contralateral hand to the electric stimulation, by means of an adhesive surface electrode. All offline analyses will be performed using the EEGLAB toolbox [34] and Matlab2016a (The MathWorks Inc). The findings will be additionally investigated by applying a Laplacian filter and a mastoidal re-referencing [35]. Then, the EEG signals will be resampled (128 Hz) and epoched into 6-s windows (1 second before and 5 seconds after the MNS). We will compute the ERD/ERS% using the “band power method” [36]. Additionally, SEP will be calculated by averaging epochs extracted from 0.25 to 0.5 with respect to the electric shock.

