## Results

### Evaluation Criteria

#### Primary End Points

A total of 30 patients will be involved in the STIM-MOTANA protocol. We will compute the amplitude of ERD/ERS modulations before and after each MNS during the different phases of anesthesia at 2 different times: when the patient is awake before surgery and under general anesthesia. The primary evaluation end point will be the amplitude of the ERD. According to the Pfurtscheller method, ERD/ERS modulations will be calculated using a baseline taken before each stimulation [36]. The changes in ERD/ERS during MNS according to the various propofol concentrations will be continuously monitored. To compare the motor EEG signal before and after injection of the anesthetic product, we will apply paired statistical tests (Student *t* test).

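### Averaging the extreme ERD and ERS of each single stimulation leaves an offset when there is no response, and that offset can change with the background EEG

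*Protocol article*

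**What the plan says.** The order of operations is set out in the protocol article under Statistics. First: "For each patient and each MNS, the maximal value of ERD and ERS max will be, respectively, selected in" the windows "0.25;0.5) seconds and (2;4) seconds after stimulation". Then: "An average over the ERDs max and ERSs max will be performed for each concentration". Then the test: "These 2 values will be, respectively, compared with average ERDs max and ERSs max obtained in the preoperative rest condition with a Student" t test at the 0.05 level. Primary End Points makes ERD amplitude the primary end point, says that the tests are paired, and states that "ERD/ERS modulations will be calculated using a baseline taken before each stimulation". EEG Data Acquisition gives the signal handling: "resampled (128 Hz) and epoched into 6-s windows (1 second before and 5 seconds after the MNS".

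The Introduction gives the first objective as verifying that stimulation-induced ERD and ERS can be detected at anesthetic propofol concentrations. The Discussion concedes that they may vanish at deep levels. The surrogate permutation test in Statistics is introduced for displaying the spectral maps. No stimulus-free reference is described for the averaged maxima.

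**The concern.** Band power from a single stimulation fluctuates strongly. Its lowest point in one window and its highest point in another are selected values, so their expectations are not zero when the stimulus has no effect. Averaging many such extremes gives a precise estimate of a biased quantity.

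Two things are at stake. If the response disappears under propofol, the endpoint can still read as an ERD and will read as an ERS, so its value does not answer whether a response is present. And the size of the offset depends on the statistical character of the background rhythm. If that differs between the awake and anesthetized recordings, the paired contrast mixes a change in reactivity with a change in background.

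**Working it through.** The article states no effect size, standard deviation or power for this endpoint, so there is no figure of its own to reproduce. The check is a simulation.

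**Inputs from the article.** Sampling 128 Hz; baseline up to 1 s before the stimulus; ERD window 0.25-0.5 s (0.25 × 128 = 32 samples); ERS window 2-4 s (2 × 128 = 256 samples); "EEG mu (7-13 Hz) and beta (15-35 Hz) bands" (Introduction); 30 patients; level 0.05.

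**Assumptions.** Smoothing of band power 0 to 0.5 s; background 1/f, with variants; two-sided test; 60 stimulations per condition. The article gives none of these.

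**Formulas.** For stimulation i with smoothed band power P_i(t) and baseline mean B_i, R_i(t) = 100 × (P_i(t) − B_i) / B_i.
- Planned: ERD = mean over i of [min of R_i in 0.25-0.5 s]; ERS = mean over i of [max of R_i in 2-4 s].
- Alternative: average P_i(t) and B_i over i first, then take 100 × (window mean of averaged power − averaged baseline) / averaged baseline.

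The expected minimum of a fluctuating trace lies below the minimum of its expectation, and the expected maximum lies above. Hence the planned order has an offset.

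**Step 1. No response, steady 1/f background, planned order (4,000 stimulations per setting).**

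| Smoothing | Mu ERD | Mu ERS | Beta ERD | Beta ERS |
|---|---|---|---|---|
| 0 | -99.6% | +763% | -99.7% | +838% |
| 0.125 s | -57% | +323% | -53% | +180% |
| 0.25 s | -33% | +207% | -31% | +108% |
| 0.5 s | -12% | +122% | -14% | +63% |

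A separate run of 6,000 stimulations gave -56/-32/-8% (mu ERD) and +319/+205/+126% (mu ERS) at 0.125/0.25/0.5 s. With the alternative order and steady-amplitude backgrounds, ERD is between -2% and +1% and ERS between -1% and +2%.

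**Step 2. Role of the baseline.** At 0.25 s smoothing in mu, a pooled baseline with per-stimulation extremes gives -43% and +160%, against -33% and +207% with each stimulation's own baseline. So the single-stimulation baseline pulls values upward: it partly offsets the false ERD and enlarges the false ERS. Pooling the baseline alone does not remove the offset. Dropping the extreme alone does not either: single-stimulation window means with own baselines read +18% (ERD window) and +20% (ERS window).

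**Step 3. Different background, still no response (mu, planned order).**
- Narrow 10.5 Hz peak added: ERD moves from -57% to -35% (0.125 s) or from -33% to -21% (0.25 s); ERS at 0.25 s moves from +207% to +257%.
- Strong slow amplitude fluctuation: ERD becomes -12% (0.125 s) or +33% (0.25 s); ERS becomes +1693% or +1185%.
- Overall amplitude × 0.3 or × 3: no shift, because R_i is a ratio.
- In beta at 0.125 s, the 10.5 Hz peak lies outside the band and ERD barely moves (-52.7% against -53.7%).

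**Step 4. Paired t test, 30 patients, no response in either condition, mu, 0.125 and 0.25 s smoothing, 60 replicates.** Monte Carlo margin at 5%: 1.96 × √(0.05 × 0.95 / 60) ≈ 0.055, about ±6 points.

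| Change in background | Planned ERD | Planned ERS | Averaging first, either measure |
|---|---|---|---|
| Narrow peak | 100% | 68-100% | 2-10% |
| Amplitude fluctuation | 100% | 100% | 3-12% |

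A pure amplitude change (× 0.3) gave 3-8% rejection with the planned measure, consistent with nominal.

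**Step 5. Sensitivity to a true 40% ERD (60 stimulations per mean).** Mu contrast with no response, planned against averaging first: 17 v 39 points at 0.125 s, 27 v 40 at 0.25 s, 34 v 38 at 0.5 s. Standardised: 3.4 v 4.7, 4.1 v 5.0, 5.1 v 6.0 in mu; 6.3 v 8.3, 7.9 v 9.0, 9.8 v 10.7 in beta. The loss runs from 1 − 9.8/10.7 ≈ 8% to 1 − 3.4/4.7 ≈ 28%.

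**The case against.** The strongest reply is that the planned test compares each concentration with the preoperative recording, not with zero, so a constant offset cancels. That stands. A reader might infer that pure noise will pass the planned test; the article does not support this, because two recordings with the same background and no response reject at about the nominal rate. The reply fails only where the background differs in within-band spectral shape or amplitude variability.

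Second, the size rests on smoothing that the article does not give. It relies on a cited band power method and an earlier protocol, and a condensed article may leave such detail there. This also stands. A reader might infer that a large false ERD is certain for the primary end point. It is not: the false ERD is small at 0.5 s smoothing and can turn positive when amplitude fluctuates. The false ERS is large throughout, but ERS is not named as the primary end point.

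Third, a reader might take the raw contrast of 17 v 39 points to mean that more than half the power is lost. The peak measure also has the smaller standard deviation, so the standardised loss is about 8-28%; between-patient variation was not simulated and would alter this.

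Fourth, classification of stimulation against rest and the permutation tests with false discovery rate correction also bear on detectability. They do, but they do not calibrate the averaged maxima or the t test.

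Finally, the selection could be read as applying to a condition rather than to a single stimulation. The article elsewhere uses the same phrase for single stimulations and averages a plural set of maxima, so this reading is unlikely. Under it the offset shrinks but depends on the number of stimulations: null mu ERD at 0.125 s is -16/-10/-5% and ERS +46/+24/+12% for 20/60/200. The article gives no number per concentration, so the wording would still need correcting.

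**Conclusion.** The point holds in a bounded form. As written, the endpoint is biased away from zero when there is no response: about -57% to -8% for ERD and about +60% to +320% for ERS, given smoothing of 125-500 ms and a steady 1/f background. It cannot by itself show that a response is present under propofol.

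The awake-versus-propofol contrast can be confounded by a change in within-band spectral shape or amplitude variability. It is not affected by a change in overall amplitude, so it would be wrong to say that any change in background EEG shifts it. The article contains no figure on how the two backgrounds differ. The rejection rates above therefore show what the assumed changes would do; they do not forecast this trial. The loss of sensitivity is real but modest.

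Because this is the primary end point and the remedy is cheap, the rule should be changed before the data are analyzed.

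**What to change.** For each patient and condition, average band power over stimulations first, form ERD/ERS% against the baseline averaged over the same stimulations, and use the mean over 0.25-0.5 s and 2-4 s as the endpoint. Both steps are needed, since pooling the baseline or dropping the extreme alone leaves a bias. State the smoothing and the frequency band with the rule.

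If peaks are kept, subtract the same statistic computed on an equal number of stimulus-free pseudo-epochs from the same recording and concentration. Each must cover 1 s of baseline plus 4 s, so 5 s free of stimulation. The 2-second resting window planned for classification is too short for this.

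The cost is a change of wording and a few lines of code, with no new data and no patient burden. Reported amplitudes will be smaller and less comparable with earlier peak-based results. The averaged measure is not perfectly null either: under strong slow amplitude fluctuation it read +4% to +7% for ERD and 0% to +2% for ERS.

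### Picking the extreme ERD and ERS from each single stimulation before averaging builds a noise floor into the primary value and distorts the size of its contrast with the awake state

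*Protocol article*

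**What the plan says.** In the protocol article, the Statistics section fixes how each value is obtained: "For each patient and each MNS, the maximal value of ERD and ERS max will be, respectively, selected in (0.25;0.5) seconds and (2;4) seconds" after the stimulation. The averaging comes next: "An average over the ERDs max and ERSs max will be performed for each concentration". The two averages are then "compared with average ERDs max and ERSs max obtained in the preoperative rest condition with a Student" t test. Under Primary End Points, "The primary evaluation end point will be the amplitude of the ERD", and the test is described as paired. The same section says that "ERD/ERS modulations will be calculated using a baseline taken before each stimulation".

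The EEG Data Acquisition section adds that "the EEG signals will be resampled (128 Hz") and "epoched into 6-s windows (1 second before and 5 seconds after the MNS"). It names the band power method but gives no smoothing width. The Introduction gives the first objective as verifying that the ERD and ERS patterns evoked by stimulation can be detected at anaesthetic propofol concentrations. The Statistics section says that processing will resemble that of the earlier MOTANA protocol, which is not shown.

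**The concern.** Averaging removes noise only if it is done before the extreme is selected. Single-trial band power fluctuates widely, so the lowest point of any quarter-second stretch lies well below its mean, and the highest point of any two-second stretch lies well above it, whether or not the cortex responded. The mean of such extremes settles on the expected extreme of noise plus signal. It does not settle on the response.

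Three things are at stake:
- The primary value does not read zero when the response has gone. That outcome matters here, because the Discussion names disappearance of ERD/ERS at deep anaesthesia as the main limitation.
- The size of a true change is misreported: ERD change is shrunk and ERS change is enlarged.
- The floor depends on how fast background power fluctuates. A change of background between awake and propofol EEG can therefore look like a change of response.

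**Working it through.** **Inputs from the article.** ERD window 0.25-0.5 s, ERS window 2-4 s, 128 Hz, one second of pre-stimulus signal, and the "EEG mu (7-13 Hz) and beta (15-35 Hz) bands over the motor cortex". At 128 Hz the windows hold 128 × 0.25 = 32 and 128 × 2 = 256 samples.

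**Assumptions not in the article.** Gaussian background noise, smoothing width, true responses (ERD -40%, ERS +50%), and any change of background under propofol. The article states no expected ERD/ERS value, SD or power, so there is no figure of its own to reproduce.

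**Formulas.** With power P_i(t) after stimulation i and reference power R, let E_i(t) = 100 × (P_i(t) - R)/R. A power drop is negative, so the maximal ERD is the window minimum.
- As written: (1/n) Σ_i min_t E_i(t). As n grows this tends to E[min_t E_i(t)], which cannot exceed min_t E[E_i(t)] and lies below it when trials are noisy. The gap does not depend on n.
- Alternative: 100 × (mean of P over stimulations and window - mean R)/mean R. This tends to the true mean change in the window.

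**Rule as written, ERD in %, reference power pooled over trials:**

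| Smoothing | Mu, no response | Mu, true -40% | Mu contrast (true 40) | Beta, no response | Beta, true -40% | Beta contrast (true 40) |
|---|---|---|---|---|---|---|
| 125 ms | -64 | -78 | 14 | -55 | -73 | 18 |
| 250 ms | -42 | -65 | 23 | -35 | -60 | 25 |
| 500 ms | -21 | -51 | 30 | -16 | -48 | 32 |

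**Rule as written, ERS in %:**

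| Smoothing | Mu, no response | Mu, true +50% | Mu contrast (true 50) | Beta, no response | Beta, true +50% | Beta contrast (true 50) |
|---|---|---|---|---|---|---|
| 125 ms | 259 | 435 | 176 | 165 | 298 | 133 |
| 250 ms | 158 | 281 | 123 | 95 | 193 | 98 |
| 500 ms | 90 | 181 | 91 | 54 | 132 | 78 |

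Repeat runs differ by about 1 to 3 points (for example -43% and -23% for mu ERD at 250 and 500 ms, and 31 points for the 500 ms mu contrast).

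**Each stimulation's own one-second baseline instead.** The ERD floor is -57%, -31% and -7% in mu and -52%, -32% and -12% in beta. The mu contrast is 74 - 57 = 17, 58 - 31 = 27 and 42 - 7 = 35 points. The floor is smaller, but it is still there and the contrast is still compressed.

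**Fixed-window mean on the same data.** Within about 1 point of 0 with no response. With the responses above it gives -36% to -40% for ERD (-36% only at 500 ms) and +49% to +51% for ERS.

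**Paired contrast with no response in either state, 30 simulated patients:**
- Same background: ERD difference -0.4 points, t = -0.3. The floor cancels.
- Narrower rhythm within 7-13 Hz under propofol: ERD +13 points (t = 10.1), which looks like a loss of ERD, and ERS -29 points (t = -4.5). The window mean stays near 0.
- Waxing and waning amplitude: ERS +75 points (t = 6.9), ERD -1 point (t = -0.9).
- By smoothing, an assumed narrowing to 9-11 Hz gives a false mu ERD difference of about 22 points at 125 ms, 8-10 at 250 ms and 0 at 500 ms.

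**Loss of standardised ERD contrast, -40% against 0, as written versus window mean.** At 250 ms: mu 0.68 against 0.78 (1 - 0.68/0.78 = 13%), beta 1.17 against 1.34 (13%). At 500 ms: mu 0.81 against 0.90 (10%), beta 1.55 against 1.69 (8%). At 125 ms the loss is 21-25%.

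**The case against.** A reader might infer that the trial is bound to conclude that the response persists under propofol. The article does not support that. It plans no test of the averaged maxima against zero; the only stated test on them compares awake with propofol. It also has other tools that bear on presence: spectral maps with a surrogate permutation test and false discovery rate correction, and classifiers of stimulation against rest. Neither uses the single-trial maxima. This stands. Its limit is that the permutation test is given for visualising the maps, and the article does not say that it decides the first objective.

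A reader might also infer that the t test will usually be falsely significant. A 10-point artefact would be significant in 94% of trials of 30 patients if the SD of paired differences were 15 points, but in 75% at SD 20 and 42% at SD 30. All of these presuppose a spectral narrowing and a smoothing width that the article does not give. With the same background in both states and no response, the floor cancels.

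The compression is also less harmful to the test than the point sizes suggest, because the spread shrinks too. The most striking results (ERD -100% in every trial, no contrast left) require no smoothing at all, and the sources for the processing are not shown.

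Finally, the extreme might be meant to be taken on the trial-averaged curve. That would shrink the floor: with no response, 125 ms smoothing and 50 stimulations, to -13% ERD and +27% ERS in mu, and at 200 stimulations to -6% and +13%. But the wording picks one value per stimulation and then averages those values. If the averaged curve was meant, the sentence still needs changing.

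**Conclusion.** The point holds as a should-fix. The stated order of operations gives a biased primary value. With reference power free of single-trial noise, the ERD floor with no response is about -64% to -23% in mu and -55% to -17% in beta over 125 to 500 ms smoothing. With each stimulation's own baseline it is smaller, down to -7% in mu at 500 ms. The averaged maxima therefore cannot by themselves establish presence or absence of the response.

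A true 40-point ERD loss reads as about 14 to 31 points in mu. A true 50-point ERS contrast is inflated, to about 91-176 points in mu and 77-133 in beta. Compression is thus the right word for ERD only.

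The planned paired test loses about 8-14% of its standardised ERD contrast at 250-500 ms, and more with less smoothing. It gives a false difference only if the spectral or amplitude structure of the background differs between awake and propofol EEG. The sizes rest on the assumed noise model and smoothing. The existence of the floor follows from the order of selection and averaging.

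**What to change.** In the Statistics section, replace the per-stimulation maximum. Average band power over all stimulations of a patient at a given concentration, take the mean over the fixed window (0.25-0.5 s for ERD, 2-4 s for ERS), and express it as a percentage change from the mean reference power. Name this ERD value as the primary end point under Primary End Points, and state the smoothing width.

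Keep the averaged single-trial maxima as a descriptive or sensitivity analysis, for comparability with earlier work.

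A sham-trigger reference scored by the same rule is optional, and only possible where the recordings hold enough stimulus-free EEG at a concentration. The article gives no interval between stimulations and has stimulation delivered discontinuously throughout surgery, so this cannot be presumed.

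The main change is one of wording and needs no new data. Its small cost is that amplitudes will be smaller than peak values reported earlier.

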These preliminary results also showed that propofol sedation (at 0.5 µg/mL and 1 µg/mL) has no negative impact on the ability of an MNS-based BCI to detect MI. Concretely, at relatively low concentrations, ERD/ERS patterns are still present in the sensorimotor cortex [26]. From these encouraging results, we intend now to verify that the oscillatory activity generated by the MNS remains present during general anesthesia with higher concentrations of propofol. This is in line with the existing literature, suggesting that the detection of MNS under general anesthesia can be achieved as somatosensory cortex maintains a certain activity confirmed by the presence of evoked potentials during sleep or general anesthesia-induced unconsciousness [27]. The cortical regions may still be receptive to information, but their ability to communicate with other regions may be altered during general anesthesia [28]. According to our knowledge, no study has investigated the way in which the cerebral motor activity was modulated with peripheral nerve stimulation over the sensorimotor cortex during general anesthesia. The aim of this study is to verify that ERD/ERS following MNS is still present and detectable under high doses of propofol with the EEG technique. Such new knowledge will enable the design of an innovative BCI specialized in the detection of intraoperative awareness during general anesthesia.

The first objective of this study is to verify that ERD and ERS patterns induced by MNS can be detected in the cortical motor EEG signal under various concentrations of propofol corresponding to the anesthetic doses required for general anesthesia. The secondary objective is to characterize and understand how the ERD and ERS generated after each MNS will be altered according to each concentration of propofol at the effect site. These results will be discussed in relation to previous results obtained from a protocol investigating the effect of light propofol sedation on EEG signals in the motor cortex. The third objective is to analyze EEG signals offline and try to detect MNS under propofol with new machine learning algorithms. Complementary, the short and middle latency components of the somatosensory evoked potentials (SEPs) will be analyzed for different propofol concentrations. Finally, the long-term goal is to design a BCI that can detect intraoperative awareness during general anesthesia.

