Consent collection	N/A^a^	N/A	N/A	N/A
Consent confirmation	N/A	N/A	✓	N/A
Providing information documents	✓	N/A	N/A	N/A
Checking inclusion and exclusion criteria	✓	N/A	✓	N/A
Medical interview	✓	✓	✓	N/A
Clinical examination	✓	✓	✓	✓
Electroencephalographic recording	N/A	N/A	✓	✓
Electromyography recording	N/A	N/A	N/A	✓
Median nerve stimulation	N/A	N/A	✓	✓
Adverse event collection	N/A	N/A	N/A	✓

^a^N/A: not applicable.

^b^d-day: day of experimentation.

Table 1 shows the registration, intervention, and evaluation schedule.

Considering the SEP stimulation, we consider that nonpainful stimuli will consist of square electrical pulses of 0.2 milliseconds of duration, generated by Micromed device Sd Ltm Stim Energy (Micromed) and delivered through a pair of grass gold cup electrodes (cathode [−] placed proximally) to the right/left median nerve at the wrist [32]. The intensity will be adjusted for eliciting visible small thumb twitches and without exceeding 50 mA.

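### Fixed scoring windows leave 0.5-2.0 s after the stimulus out of the tested ERD and ERS amplitudes, so a substantial shift in timing under propofol could be taken for disappearance

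*Protocol article*

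**What the plan says.** In the protocol article, Methods, Statistics, the ERD and ERS maxima for each patient and each stimulation are, respectively, "selected in (0.25;0.5) seconds and (2;4) seconds after stimulation". The section supports these windows by citing literature. It then states: "An average over the ERDs max and ERSs max will be performed for each concentration". The averages are compared with the preoperative ones by Student t test. No change of window with concentration is described. Primary End Points names ERD amplitude as the primary end point.

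For the offline classifiers, the same section says: "The motor task time window will begin 0.5 seconds after the MNS". Each trial is cut into "a motor task time window and a resting time window, both lasting 2 seconds", so the active window is 0.5-2.5 s.

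Study Design describes the stimulus as "square electrical pulses of 0.2 milliseconds of duration". Under EEG Data Acquisition the signal is "epoched into 6-s windows (1 second before and 5 seconds after the MNS". The Introduction's first objective is whether the patterns can still be detected at anesthetic concentrations. The second is to "characterize and understand how the ERD and ERS generated after each MNS will be altered according to each concentration of propofol".

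**The concern.** The amplitude score and the classifier address the response to the same brief pulse but look at largely different times. Three quarters of the classifier's active window lies where neither amplitude score looks.

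A window fixed across concentrations also assumes that the response does not move. The article gives no basis for that at anesthetic concentrations. Its Introduction says that, to the authors' knowledge, no study has examined how motor cortical activity is modulated by peripheral nerve stimulation during general anesthesia. The preliminary propofol data it reports stop at 1 µg/mL. Statistics plans tests of latency for the evoked potentials but states none for ERD or ERS.

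If propofol shifts the response enough, the t test records a fall in amplitude. Principal Findings names disappearance at deep anesthesia as the main limitation of the study. The tested amplitude cannot separate that outcome from a substantial delay, which bears on the first objective (still present?) and the second (how altered?).

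**Working it through.** The article states no figure for this point that could be reproduced. The check is interval arithmetic on the stated windows, followed by an illustration under assumed response shapes.

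**Inputs from the article:** ERD window 0.25-0.5 s; ERS window 2-4 s; classifier active window 0.5 s to 0.5 + 2 = 2.5 s; epoch -1 to +5 s.

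**Interval arithmetic**
- Unscored gap: 2.0 - 0.5 = 1.5 s.
- Scored share of the post-stimulus epoch: (0.25 + 2)/5 = 45%.
- Classifier window and ERD window: overlap 0 s.
- Classifier window and gap: 1.5 s, and 1.5/2 = 75%.
- Classifier window and ERS window: 2.5 - 2.0 = 0.5 s, and 0.5/2 = 25%.

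**Share of a shifted peak that is still scored.** Assume a noiseless bell-shaped response with SD s. If its peak lies a distance d outside the window, the largest value inside is exp(-d²/(2s²)) of the true peak. Peak times and s are assumptions; the article gives neither.

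| Response, peak time | d (s) | s = 0.1 | s = 0.2 | s = 0.4 |
|---|---|---|---|---|
| ERD, 0.15 s (early) | 0.10 | 61% | 88% | 97% |
| ERD, 0.375 s | 0 | 100% | 100% | 100% |
| ERD, 0.6 s | 0.10 | 61% | 88% | 97% |
| ERD, 0.75 s | 0.25 | 4% | 46% | 82% |
| ERD, 1.0 s | 0.50 | 0% | 4% | 46% |
| ERD, 1.5 s | 1.00 | 0% | 0% | 4% |
| ERS, 1.0 s | 1.00 | 0% | 0% | 4% |
| ERS, 1.5 s | 0.50 | 0% | 4% | 46% |
| ERS, 1.75 s | 0.25 | 4% | 46% | 82% |
| ERS, 3 s | 0 | 100% | 100% | 100% |

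**Prolonged ERD.** A plateau that starts at 0.25 s and lasts to 1, 2 or 3 s is scored at 100% in the ERD window. If it lasts to 3 s it also fills half of the ERS window, (3 - 2)/2, and could lower the ERS score.

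**Noise floor.** The score is a mean of per-stimulation maxima, so it stays above zero with no response at all. In a simulation with smoothed white noise at 128 Hz (an assumed noise model), it was about 1.3 noise SD in the ERD window and 2.4 in the ERS window. The longer the window, the higher this floor.

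**The case against.** Five points can be made for the plan.

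1. Fixed, prespecified windows protect against choosing them after seeing the data, and the article says they follow published work. This stands as a reason to keep them. The cited sources cannot be seen here, so whether they suit a brief pulse is open. By the article's own account they cannot settle timing under general anesthesia.

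2. The time course is examined elsewhere. Statistics plans spectral perturbations with a permutation test and false discovery rate correction, with no stated restriction to the two windows. That analysis and the classifier can both show activity at 0.5-2 s. This is real mitigation. It does not change what the tested amplitude measures, and the article does not say which result prevails if they disagree.

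3. An amplitude score and a classifier need not share a window. True: the mismatch is not a contradiction. It is an unexplained difference about where the response is expected.

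4. A reader might infer that any early, delayed or prolonged response is lost. The documents do not support that. A prolonged ERD is still scored in its own window, and an early ERD at 0.15 s keeps 61-97%. Nor does a 0.25 s delay necessarily move an ERD centred at 0.375 s out of reach. Its peak would be at 0.625 s, so d = 0.125 s, and exp(-0.125²/(2s²)) gives 92% at s = 0.3 and 97% at s = 0.5.

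5. A reader might also infer that the ERS score misses most of the awake rebound. That requires the rebound to peak before 2 s, which the article does not state. The ERD window is where the maximum is taken; it does not imply that the ERD ends by 0.5 s.

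**Conclusion.** The concern holds in a limited form. It is certain from the article that 1.5 s between the two scoring windows is left out of the tested amplitudes, that the same windows serve every concentration, and that the classifier window has no overlap with the ERD window and lies 75% in the gap.

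It follows that the primary amplitude can confuse a substantial delay with a loss. The size depends on the assumed response width: 4-82% retained for an ERD peaking at 0.75 s, 0-46% at 1.0 s, and 0-46% for an ERS peaking at 1.5 s. The consequence is attenuation, at worst to the noise floor. Whether propofol shifts the response at all is unknown. The point is therefore a safeguard against a wrong conclusion of disappearance, and it does not show that the present windows will give one.

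**What to change.** - Keep the prespecified windows as the main amplitude score. Justify them for a brief pulse, and either reconcile them with the classifier's 0.5-2.5 s window or explain the difference.
- At every concentration and in the awake condition, add peak latency and amplitude from the concentration-averaged ERD/ERS curve over 0-4 s. Alternatively, use a whole-epoch permutation test built on the spectral-perturbation analysis already planned.
- Conclude that a response is absent only if it is absent over the whole span, not merely in its fixed window.
- If the windows are re-set, fix them before the anesthetized data are opened, and acknowledge that choosing them on awake data favours the awake condition and can itself produce an apparent fall.

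Simply extending the per-stimulation ERS maximum back to 0.5 s is a weaker remedy. It lengthens the window from 2 to 3.5 s and raises the noise floor.

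The cost is analysis wording and slightly more analysis; the existing -1 to +5 s epochs already hold the data. Whole-span peaks are noisier than fixed-window ones, so they should stand beside the main score and not replace it.
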